#### Data management and availability

The study complies with the General Data Protection Regulation (GDPR) and Data Protection Act 2018, which require data to be de-identified as soon as it is practical to do so. All data samples to be collected as part of this study will be anonymised with participants being assigned a unique study code. Any information pertaining to personal details will be kept in locked filing cabinets in the biomechanics laboratory Northumbria University and is only available to research staff directly running the study. All data will be entered into an electronic database using unique study codes for each participant and securely stored on a password-protected computer database. Any significant protocol modifications during this study will be communicated to the trial registry. Data will be available from the study, once conducted, upon reasonable request from the principle investigator (SS). Results will be disseminated through academic outputs (e.g., national, and international conferences and publications).

## Discussion

There is a growing need for simple, valid, reliable, and objective methods to evaluate the running gait away from the laboratory within real-world environments, yet with the availability of such a wide range of research-grade, commercial and high-end multimodal wearables users may find it difficult to select the most suitable [21]. Therefore, through evaluating validity and reliability of various grades of wearables and demonstrating their efficacy and usability in applied studies, this protocol seeks to enhance the understanding of wearables for objective measurement of running gait.

### Analytical validation

This pilot study protocol was developed in response to recently reviewed evidence and study recommendations for assessing gait in ecologically valid environments [54]. Prior to applying wearables to sporting contexts it is critical to examine the validity and reliability of such technology. This proposed protocol will assess the validity and reliability of different grades of wearables (research-grade, commercial, novel multimodal) for running gait assessment, examining outcomes against ‘gold-standard’ reference measures (3D motion capture). Research-grade wearable devices have been developed by academic researchers, but few have been used in applied studies to inform clinical or performance decisions [21]. Similarly, despite the widespread use, fewer than 10% of commercially available wearables are validated against an accepted ‘gold-standard’ [27]. Reliability studies of wearables for running gait are less established [21]. An important implication of this study is that it is expected to provide the first evidence on the accuracy and reliability of using a multi-modal wearable device (DANU Sports System) during running gait, which will help develop the standard of wearables. At present, most wearables are limited in their assessments to only examination of selective spatiotemporal or kinematic outcomes, for example step frequency, step length, tibial acceleration and ground contact time are commonly cited [21]. Despite numerous studies establishing that running biomechanics cannot be described based on a single parameter [55–58]. Therefore, the use of a multi-modal system (e.g., combination of IMU and pressure insoles, or accelerometer and pressure insole) as proposed in this protocol will address such limitations and allow for more comprehensive assessment of running gait.

### Exploratory clinical validation

Following the examination of analytical validity and reliability the protocol will seek to examine runners in a more natural running environment to provide initial evidence on clinical (or performance) validity (i.e., do the analytically valid outcomes provide something meaningful). By moving beyond the laboratory to more natural running environments (i.e., indoor, or outdoor running tracks, or sports venues), we will be able to evaluate whether the different grades of wearables (research-grade, commercial, novel multimodal) acceptably measure and provide meaningful insight in the specified context of use [23]. This study will determine what grade of wearable may be necessary to provide meaningful data on real-world running. The use of sub-group analyses will elucidate outcomes that are most representative of an individual’s running gait, as well as reveal the interactions between confounding demographic factors, injury status and performance level aid performance enhancement and reduce injury risk / occurrence [59–61]. The proposed protocol will allow for examination of such factors and hopes to provide clarity for researchers and practitioners on the applicability of certain wearables in context.

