#### Real-World environment testing

Data from the novel multimodal, commercial, and research-grade wearables will be collected within real-world environments to test the clinical / performance validity of the wearables (i.e., can they differentiate or provide meaningful data on relevant populations). Recruitment for the real-world environment testing began in June 2023 with an expected end date October 2023.

*Participants*. Within the real-world environment testing 40 individuals, specifically novice/amateur (n = 20) and expert/sub-elite (n = 20) running performance level. Performance level will be based on their 5km running time (i.e., age graded performance % [35]).

*Wearable location*. Each participant will be equipped with the DANU Sports System (socks on both feet), two Axivity AX6 sensors attached to the shoelaces and two DorsaVi ViMove2 sensors on the tibia.

*Running procedures*. All participants, regardless of performance level, will be asked to complete a 5km run on a standardised route in North-East England. The course will be run on a mixture of trail paths and concrete paths, with 174ft elevation gain throughout. Information about conditions (e.g., environment and shoes) and objective load data (e.g., time and pace) will be collected. Participants will wear their own running shoes.

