### Statistical analysis

#### Analysis common to all studies

The statistical analysis will be performed using statistical software SPSS 25 (SPSS Inc., Chicago, Illinois, USA). Demographic characteristics will be summarised using descriptive statistics, including mean, standard deviation, median, minimum, maximum, and inter-quartile range for continuous or ordinal data and percentages for categorical data. The descriptive statistics will be tabulated and presented graphically for clarity. All data will be checked for normality distributed with Shapiro-Wilks tests before conducting parametric tests. Non-normal continuous distributions will be transformed where appropriate to meet the requirements of parametric tests; otherwise, the equivalent non-parametric tests will be adopted. Data will also be assessed graphically (such as histograms or scatter plots) for clarity of information. Statistical significance will be determined at p < 0.05 unless otherwise stated. Due to the experimental nature and novelty of the work and wearable systems, we will not control for multiple comparisons in order to avoid a Type II error.

*Analytical validation analysis*. To examine analytical (concurrent) validation of the wearable devices (research-grade, commercial, novel multimodal) for running gait measurement, we will compare outcomes to relevant reference measures (i.e., force plates for ground contact time) in all laboratory testing participants (n = 40). To compare running gait outcomes from the wearables and reference systems, the absolute difference, Pearson’s correlation (r), intraclass correlations (ICC), the level of agreement through the Bland Altman plots, and 95% Limits of agreement (LoA) will be calculated [48]. Accuracy will be evaluated in terms of root mean squared errors (RMSEs).

To determine test re-test reliability of the wearables, r, and ICCs between the two testing time-points will be calculated [49]. A predefined ICC performance scale will be used, defined as poor (<0.50), moderate (0.50–0.75), good (0.75–0.90) or excellent (>0.90) [50]. ICC is a common statistic for evaluating repeatability and is needed to calculate the minimally detectable change (MDC) [51, 52]. The standard error of measurement (SEM) and standard deviation (SD) will also be calculated. Laboratory based analytical validity and reliability outcomes will be descriptively reported and discussed across research-grade, commercial and novel multi-modal wearable devices.

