To examine the analytical (concurrent) validation of running gait outcomes measured in real-world settings from the various grades of wearables in all real-world testing participants (n = 40), we will compare outcomes across the wearable devices (research, commercial and novel multi-modal) through widely used measures of agreement. The absolute difference, r, ICC, the level of agreement through the Bland Altman plots, 95% LoA, RMSEs will be calculated to evaluate agreement between outcomes generated by each wearable [48].

*Exploratory clinical validation analysis*. To provide an initial exploration of clinical (performance) validation, we will investigate group difference and relationships with clinically (or performance) relevant measures. For group differences (e.g., previous injury history or performance level), analysis of co-variance (ANCOVA), will be conducted to assess for differences between groups (injured vs non-injured, or elite vs novice) in the individual running gait outcomes (e.g., ground contact time etc.) from the novel multimodal, commercial and research-grade wearable devices during the running tasks, while controlling for demographics that are significantly related to the running gait outcomes. Relationships between running gait outcomes and demographic variables (e.g., sex, age, height, weight etc.) within groups (injured vs non-injured, or elite vs novice) will be completed through Pearson correlations within each grade of wearable device (research, commercial, multimodal).

To examine the usability of the wearable devices the SUS scores for each wearable will be calculated and visualised. To investigate differences in participant perception of the usability for each grade of wearable, separate analysis of variance (ANOVA) tests will be performed. The ANOVAs will determine the differences between the SUS scores within the different device grades between participant groups (e.g., injury history, performance level). The relationships between the SUS scores, demographics (e.g., sex, age, age-grade performance), and wearables characteristics (e.g., price, weight, and battery life) will be explored using Pearson correlations [39]. The strength of the correlation will be assessed based on Cohen’s criteria: correlations < 0.30 are considered small, correlations between 0.30 and 0.50 will be considered medium, and correlations > 0.50 are considered strong [53].

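### The Discussion says the study will determine which grade of wearable may be necessary, but no planned analysis compares how well the devices separate the runner groups

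*Protocol article*

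**What the plan says.** The Discussion (Exploratory clinical validation) makes a comparative promise: "This study will determine what grade of wearable may be necessary to provide meaningful data on real-world running". The section on Real-World environment testing gives the purpose of that data collection as "to test the clinical / performance validity of the wearables (i.e., can they differentiate or provide meaningful data on relevant populations".

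The analyses that bear on this are in the Statistical analysis section:

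- **Group differences.** An ANCOVA compares groups "in the individual running gait outcomes (e.g., ground contact time etc.) from the novel multimodal, commercial and research-grade wearable devices during the running tasks", adjusted for related demographics. No device factor and no group-by-device contrast is named.
- **Relationships.** These "will be completed through Pearson correlations within each grade of wearable device (research, commercial, multimodal".
- **Usability.** ANOVAs compare SUS scores between participant groups within device grades.
- **Devices against each other, real world.** "we will compare outcomes across the wearable devices (research, commercial and novel multi-modal) through widely used measures of agreement": absolute difference, correlation, ICC, Bland-Altman limits and RMSE.
- **Devices against each other, laboratory.** Validity and reliability results "will be descriptively reported and discussed across research-grade, commercial and novel multi-modal wearable devices".
- **Criterion.** "Statistical significance will be determined at p < 0.05 unless otherwise stated", and "we will not control for multiple comparisons in order to avoid a Type II error".

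There are 20 runners per group in each arm.

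**The concern.** Which grade is necessary is a question about differences between devices. A group ANCOVA on one device has a different null hypothesis: that the groups do not differ on that device. Agreement statistics do not close the gap either. They show whether two devices give similar readings in the same runner, not which one better distinguishes a novice from an expert.

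The only group-difference evidence on grades would therefore be a set of per-device results with p-values. A significant result on one device and a non-significant one on another does not show that the devices differ, and at 20 per group such splits are easy to obtain by chance. A cheaper device could be thought insufficient, or a high-end one necessary, when the two perform equally well.

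**Working it through.** **1. What the plan's own figure supports.** The Sample size calculation calls 20 per group adequate on rules of thumb. It gives no effect size, SD or power, so there is no calculation to reproduce.

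**2. Power of one device's test.** From the documents: n = 20 per group, alpha 0.05. Assumed: two-sided test, standardised difference d, no covariates. With a two-sample t test on 38 df and noncentrality d × √(20/2):

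- d = 0.5: power 34%, so a miss rate of 100 − 34 = 66%
- d = 0.8: power 69%, miss rate 31%
- d = 1.0: power 87%, miss rate 13%
- 80% power needs d of about 0.91

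**3. How often equally good devices split.** Simulation: three devices with the same true d and the same noise, worn by the same runners, within-group correlation rho between devices, and a separate t test on each. Neither d nor rho is in the documents; both are assumptions. Entries are the chance that, of two devices, one is significant and the other is not, for one outcome:

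| rho | d = 0.5 | d = 0.65 | d = 0.8 |
|---|---|---|---|
| 0.6 | 27% | 30% | 26% |
| 0.75 | 21% | 24% | 20% |
| 0.9 | 13% | 15% | 13% |
| 0.95 | 9% | 10% | 9% |
| 0.99 | 4% | 5% | 4% |

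Outside that range of d the rates are lower: at d = 1.0 they are 5% (rho 0.95) and 2% (rho 0.99). For three devices, the chance that they do not all fall on the same side is 14% to 45% over rho 0.6 to 0.95 and d 0.5 to 0.8. Those three-device figures apply to only three outcomes (step 4).

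**4. Where a direct comparison is possible.** By Table 2, ground contact time, step frequency and symmetry come from all three devices. Step time, foot-strike pattern, flight time and tibial acceleration come from two. Step length comes from one, so it allows no comparison.

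**5. Which contrast answers the question.** A raw-scale group-by-device interaction compares mean group differences in the units of measurement. A device that is worse only because it is noisier has the same expected raw difference, so the interaction is zero. Example: runner SD 1, raw group difference 1.0, device noise SD 0.3 and 2. The standardised effects are 1/√(1 + 0.09) = 0.96 and 1/√(1 + 4) = 0.45. In simulation at 20 per group the separate tests were significant in 84% and 28% of trials. The raw contrast rejected in 5%, its null rate. A contrast on standardised values rejected in 33%.

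**6. Precision of the standardised contrast.** Approximate SE = √(2(1 − rho)) × √(2/20); 95% half-width = 1.96 × SE.

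- rho 0.5: SE 0.32, ±0.62
- rho 0.7: SE 0.24, ±0.48
- rho 0.8: SE 0.20, ±0.39
- rho 0.9: SE 0.14, ±0.28
- rho 0.95: SE 0.10, ±0.20

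The between-device difference in d detectable with 80% power runs from 0.89 (rho 0.5) to 0.28 (rho 0.95). The formula treats the SDs as known, so these intervals are slightly too narrow.

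**The case against.** The strongest reply is that the plan never says grades will be ranked by p-value. A reader might infer that they will be, because p < 0.05 is the only inferential criterion given, but no section states it. The documents offer other grounds for comparing grades: laboratory validity and reliability, real-world agreement, which outcomes each device can report at all, and practicality, cost and comfort. This stands, and the split rates above are therefore conditional on such a reading.

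A reader might also infer that the paired device data go unused. They do not: the agreement analyses are within-runner comparisons of devices. They simply do not address discrimination between groups.

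It is also fair that the listed aims do not include ranking devices by discrimination, that asking whether a device can differentiate is a per-device question, that the work is labelled an exploratory pilot, and that the Discussion sentence itself carries a hedge. These points limit the seriousness. They do not supply the missing comparison, and the exploratory label sits badly with a promise to determine. Nor is this only a modelling detail left to a separate analysis plan: the article states both its analyses and its conclusion, and the two do not match.

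Finally, the magnitude depends on assumed inputs, and d of 0.5 to 0.8 is where splits are most frequent. That stands too. Nor should the split rates be set against the 5% level as if they were inflated Type I errors: no planned test has that event as its error.

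**Conclusion.** The concern holds in limited form. The Discussion promises a conclusion about which grade may be necessary, and no planned analysis compares the devices' ability to separate the groups. If grades were judged on differing significance, two equally good devices could split on one outcome in roughly 9% to 30% of trials. This rests on 20 per group, two-sided 0.05, assumed d of 0.5 to 0.8 and assumed between-device correlation of 0.6 to 0.95; at 0.99 it falls to about 5% or less. The documents do not support saying that the plan will rank grades this way. Even the right comparison would usually give an estimate with a wide interval at this sample size, so the sentence claims more than the study can deliver. The change is cheap and worth making; it does not call the rest of the analysis into question.

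**What to change.** 1. For each outcome reported by more than one device (three outcomes on all three devices, four on two), report the paired between-device difference in standardised group effect with a 95% confidence interval, for example by bootstrapping runners within group. Do not rely on a raw-scale group-by-device interaction, which misses a device that is worse only through noise.
2. State that no grade will be called necessary or insufficient because one device was significant and another was not.
3. In the Discussion, replace *will determine* with *will provide initial estimates of*, and adjust the rest of the sentence to fit.

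The cost is one extra contrast per device pair and shared outcome on data already planned, plus two wording changes. The downside is that intervals of about ±0.2 to ±0.6 SD will make the conclusion about grades more modest.

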### Usability

Technological, design and aesthetical characteristics are key areas together that affect the adoption of wearable devices in sport [62–64]. Wearable devices such as the ones described in this paper are able to monitor the performance of the user in a cost effective, accurate and non-invasive manner, yet they are of little use if they lack practicality, comfort, and aesthetical pleasure. Hence, a necessary step is to investigate the opinions of the targeted end-users. This protocol will seek to for investigate the usability of wearables during running activity via administration of a questionnaire. With any new technology it is essential to understand user acceptance in order to predict behavioural intention to use the system in the future. Therefore, by understanding user acceptance of the three systems we can gain further insight into future usage.

### Practical implications

Understanding running gait is crucial in injury prevention and for improving performance. Creating a protocol that considers the validity and reliability of wearables for running gait assessment, consequently, allows practitioners to examine numerous key areas (i.e., fatigue, speed, surface, injury) in ecologically valid settings and without disrupting an individual’s training regime. Furthermore, the proposed protocol partly addresses some additional limitations observed in previous studies, including small sample sizes, examination of only one outcome and lack of consideration for the user’s comfort. Through using various wearables in both the lab and real-world environments, the suitability of each device not only in regard to running gait outcomes obtained but also practicality, time and cost-effectiveness, and user comfort can be evaluated.

## Conclusion

This exploratory pilot study will provide evidence for the validity and reliability of running gait as measured via wearables of various grades (research-grade, commercial, novel multimodal) in adult runners. In addition, it will provide initial evidence on the relationships between demographic factors, injury status, and performance level on objectively measured running gait outcomes from different grades of wearables.
